## Abstract

**Background:**

New Perspectives (NP) is a prevention program aiming to prevent that youth at onset of a criminal career will develop a persistent criminal behaviour pattern. The effects of NP on juvenile delinquency and other life domains are investigated, using a randomized controlled trial (RCT).

**Method/Design:**

In the present study at-risk youth aged 12 to 23 years are assigned randomly to the intervention (*N* = 90, NP) or control condition consisting of care as usual (*N* = 90, CAU). After screening, random assignment, and consent to participate, adolescents and their parents are requested to complete questionnaires. Data are collected at four points in time: at baseline (before the start of the intervention), after 3 months, after 6 months (post-test) and 1 year after treatment (follow-up). Primary outcome measures include involvement in delinquent behaviour and recidivism. Secondary outcome measures include parenting behaviour, life events, prosocial behaviour, deviant and prosocial peers, externalizing behaviour, cognitive distortions, moral reasoning, self-worth, anxiety, depression, client satisfaction, therapeutic alliance and motivation. Standardized questionnaires and interviews are used to collect data. Moderator analyses will also be conducted in order to examine the influence of ethnic background, gender and age on the program effectiveness.

**Discussion:**

The present study will provide new insights in the effects of a prevention program targeting youth at risk for the development of a persistent criminal career.

**Trial registration:**

Dutch trial register number NTR4370. The study is financially supported by a grant from ZonMw, the Dutch Organization for Health research and Development, grant number 157004006. The study is approved by the Ethics Committee of the University of Amsterdam, approval number 2011-CDE-01.

## Background

Juvenile delinquency can be considered as an important societal problem with negative consequences, such as mental health-, financial-, and work-related problems. Young offenders represent a relatively large proportion of all offenders in the justice system. For example, in 2003, juveniles in the United States accounted for 16% of all arrests (i.e., 2.3 million arrests), 15% of all violent crime arrests, 29% of all property crime arrests and 39% of all vandalism offences (Snyder & Sickmund 2006). The highest levels of prevalence rates of self-reported *total delinquency* (last year) among 12-15-year-old juveniles were found in cities of the United States, Ireland, the Netherlands and Germany (based on 43,968 respondents from 63 cities and 31 countries) (Enzmann et al. 2010). These countries also showed the highest rates of serious violent delinquency among youth. Approximately one third of the 12-to 17-year-old Dutch juveniles (38%) reported having committed a criminal offence (Van der Laan & Blom 2011).

Earlier studies showed that severe persistent delinquent behaviour of youngsters starts with minor offences and an accumulation of risk factors in multiple life domains, which could escalate in serious criminal offending (Loeber et al. 2009). In order to prevent that juvenile offenders will develop a chronic and persistent criminal career, there is a great urge for evidence-based prevention programs. Given the high costs of intensive treatment and incarceration of delinquents, investing in prevention could also contribute to economic benefits for society.

In the present study we will examine the effects of the prevention program ‘New Perspectives’ (NP), targeting juveniles at risk for the development of a persistent criminal career. This community-based program is acknowledged as a well implemented program with a strong theoretical foundation (Van den Braak & Konijn 2006). The NP program aims to prevent or reduce delinquent behaviour and offending. The theoretical framework of NP is based on the *Risk-Needs-Responsivity* (RNR) *model* (Andrews et al. 1990). Preventive and curative interventions are most likely to be effective when programs target criminogenic factors and are responsive to the individual needs of juveniles (Andrews & Dowden 2007). NP is also based on the *Transtheoretical Model of Behaviour Change* (Prochaska & Di Clemente 1984), which describes the stages of behaviour change in the context of treatment processes. Moreover, NP can be viewed as a multicomponent program addressing multiple risk factors by including multiple treatment modalities, such as elements of cognitive and problem-solving skills training and involvement of the social network (parents, peers and teachers, etc.). Multi-facetted programs integrating multiple components for parents, youths and their environment (school and community) are considered to be more beneficial than narrowly focused programs in juvenile crime prevention (McCord et al. 2001).

Previous evaluation studies of NP (Noorda & Veenbaas 1997; Geldorp et al. 2004) revealed positive results in various areas (such as school, family and peers) for NP youths. However, these evaluation studies lacked the use of a control group. Application of randomized controlled trial (RCT) provides the strongest evidence of causal relations between a participant’s exposure to treatment conditions and changes in deviant behaviour (Clingempeel & Henggeler 2002; Weisburd 2010). Therefore, the present study involves a randomized controlled trial.

On the basis of earlier international studies of programs aimed at preventing and reducing delinquency and recidivism, we expect to find evidence for positive effects of NP. Positive effects were found for diversion programs, stating that well-implemented programs, integrating behavioural and family-based change strategies, produced reductions in subsequent offences. These prevention programs targeted youth with only one or two police contacts, who have not yet exhibited a longstanding pattern of severe antisocial and delinquent behavior (Mulvey et al. 1993). Furthermore, a systematic review (Lösel & Beelmann 2003) indicated that well-structured multimodal cognitive-behavioural programs were most appropriate for preventing antisocial behaviour of adolescents. Hanlon and colleagues (2002) evaluated a multimodal and community-based prevention program, including individual counselling, mentoring and remedial education, targeting youths at risk for the development of a deviant lifestyle. This program proved to be effective in reducing delinquent activity in the long-term (1 year after the intervention). Thus, there is empirical evidence to suggest that multimodal prevention programs are effective.

However, in the international literature, there is no consensus on the degree of effectiveness of programs in preventing persistent delinquency. For example, a meta-analytic study (Deković et al. 2011) examined the long-term effects of prevention programs carried out during early and middle childhood on criminal offending into adulthood. They found no convincing evidence that early prevention programs are able to prevent adult crime. Most of the evaluation studies have focused on prevention in early or middle childhood (e.g. Deković et al. 2011) and on serious and chronic offenders (e.g. Asscher et al. 2007), but in the present study we will investigate the effects of a prevention program targeting youngsters at onset of their criminal career.

The program effectiveness of NP is examined in terms of decreased *delinquent behaviour* and *improvements* in life domains of juveniles, such as school, peers, and parents. Moreover, the study is focused on outcomes that are not directly addressed by NP, but are considered as factors related to delinquent behaviour, such as parental monitoring (Crouter & Head 2002), cognitive distortions (Barringa et al. 2000), self-esteem (Donnellan et al. 2005), and moral reasoning (Stams et al. 2006; Van Vugt et al. 2011). Given that externalizing behaviour problems often co-occur with internalizing problems (Barker et al. 2010), we also examine program outcomes related to depression and anxiety. Another important question of present study is related to the intervention effects for specific subgroups of youngsters. The NP client population in Amsterdam is very diverse with respect to ethnic background, gender and age. NP is also divided in different modalities for younger (below 16 years; NP ‘Preventief’ and ‘NP Plus’) and older adolescents (from 16 years; NP). In this respect it is important to detect possible differential effects of NP for these subgroups. In social work research and practice, there is little consensus about the need for, and effectiveness of, ethnically, gender-and age-tailored treatment (Wilson et al. 2003; Zahn et al. 2009). Although research consistently demonstrates that female juvenile offending is associated with specific risk factors (i.e., different from those of male juvenile offending) (Hipwell & Loeber 2006), gender-non-specific programs were found to be equally effective in reducing recidivism for boys and girls (Zahn et al. 2009). Also, a large amount of studies revealed that migrant children are at increased risk of mental health problems and experience specific risks related to stress and feelings of alienation due to the migration process (Stevens & Vollebergh 2008). Despite these different risk factors, mainstream service programs were found to be equally effective for minority and white juvenile delinquents in the United States (Wilson et al. 2003). Moreover, it is well known that the extent and impact of risk factors changes with age. For instance, the influence of peers in the adolescent’s behaviour increases with age, while the impact of parental supervision decreases with age (Loeber et al. 2006; Van der Put et al. 2011). Consequently, well-founded empirical knowledge about differential effects of prevention programs for different subgroups is needed.

Moreover, we are interested in the contribution of client factors (e.g., motivation, client satisfaction), client’s expectations and non-specific treatment factors to the program effects of NP. For example, the therapeutic alliance is assumed to have a strong impact on program outcomes (Karver et al. 2006). Also several researchers have indicated that the level of client satisfaction is related to behaviour improvements (Donovan et al. 2002). However, the unique contribution of these factors to treatment success remains unclear. The interrelation of clients’ expectations, therapeutic alliance, and specific treatment method is assumed to be complex. For example, therapeutic alliance can be promoted by professional appliance of specific methodical techniques (Stams et al. 2005) and client type and severity of psychopathology have been found to be associated with client satisfaction (Nock & Kazdin 2001).

There are, in particular outside the USA, relatively few randomized experiments in the field of criminology (Farrington & Welsh 2005). Experimental designs can rule out alternative explanations for program outcomes, such as passage of time, effects of assessment, or different types of clients (Cook 2003). By using an experimental design, the present study will be able to gain more insight into the effects of NP in preventing persistent delinquent behaviour and reoffending of at-risk youth. Our study focuses on youth at the onset of a criminal trajectory, who are at risk for persistent offending. This study will also provide more information about improvements in other life areas, such as relationships of youngsters with their parents and peers. In addition, moderators will be investigated in order to enhance the effectiveness of NP for divers target groups (young and older juveniles, boys and girls, different ethnic backgrounds). Finally, we will examine the contribution of non-specific treatment characteristics, client factors and client’s expectations to the intervention effects.

## Methods and design

### Aim of the study

The aim of this study is to examine the effectiveness of the prevention program ‘New Perspectives’ (NP) in a sample of youth at risk for the development and progression of a deviant life style. The effects of NP are compared with care as usual (CAU), the comprehensive interventions that are already available. We expect that NP will be more effective than CAU. The effectiveness will be measured in terms of decreased problem behaviour and improved quality of life. Primary outcomes are defined as a reduction in delinquent behaviour, offending, and recidivism. Furthermore, we will investigate improvements in the individual domain (e.g. self-esteem and cognitive distortions) and in life domains, such as school, peers, and parents. These factors are considered as mediators for the effectiveness of NP. The role of clients’ expectations (satisfaction), client factors (motivation) and non-specific treatment (treatment alliance) variables will be taken into account as well. Finally, potential moderators (age, ethnicity and gender) of the effectiveness of NP will be studied.

### Design

This study protocol will follow the CONSORT statement (Moher et al. 2010). The design of this study involves a randomized controlled clinical trial (RCT) in which NP will be compared to CAU. Data of adolescents and their parents will be collected at four points in time: prior to treatment (T1 pre-test assessment), after 3 months (T2 the intensive intervention phase), immediately after treatment (T3 post-test assessment, 6 months after T1, the aftercare phase), and 1 year after treatment (T4 follow-up 12 months after T3).

Adolescents aged 12 to 23, who meet the eligibility criteria of NP (these criteria are described in next section) will be randomly assigned to either NP or CAU. Random assignment per adolescent will be executed by the researcher (first author) using computer generated block randomization. The ratio of the randomization between NP and CAU is 1:1. See Figure 1 for the procedure’s flow chart.

**Figure 1 Fig1:**
[figure not shown]
**Flow diagram NP effect study**
***.***

The Ethics Committee of the University of Amsterdam (Faculty of Social and Behavioural Sciences) approved the study design, procedures and informed consent. Participation is voluntary and all participants (adolescents) will be asked to provide written informed consent at first assessment. Parental consent will be obtained when the adolescent is younger than 16.

### Sample size

Power calculations indicated that 90 adolescents per condition (assuming an alpha of 0.05, 0.95 power, and a medium effect size, based on power calculations of G*Power (Faul et al. 2009)), are sufficient to detect a difference in problem behaviour at post-test. There is also sufficient power to perform moderator-analyses for different subgroups (Power > .80 to detect small effects for 2 to 8 groups). Therefore, a total of 180 adolescents and parents will be included.

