### Statistical analysis

Primary analyses will be performed according to the intention-to-treat principle (Montori & Guyatt 2001). The effect of the intervention with regard to the difference in official arrest rates (recidivism) between the experimental and control group will be examined using logistic regression analysis and survival analysis. The primary (involvement in delinquency, SRD) and secondary continuous measures will be analyzed with ANCOVA using the outcome measures at post-test and follow-up as dependent variables, treatment condition as factor and pre-test scores as covariates.

Moderator analyses will be conducted using two-way ANCOVA’s with the moderators and treatment condition as factors, to examine interaction effects. For each questionnaire, the effect size is computed as Cohen’s *d*, based on adjusted means and standard errors, with a positive sign indicating improvement in the NP group relative to the control group. Mediator effects will be analyzed using structural equation modelling.

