## Discussion

This article describes the study protocol of a program evaluation of the prevention program ‘New Perspectives’ (NP). This study is one of the few randomized clinical trials in Europe examining a program targeting youth at risk for the development of a persistent criminal career (Farrington & Welsh 2005). By conducting an experimental research strategy (RCT) we will be able to control for confounding effects more accurately than in studies with other designs. Furthermore, there are several strengths with regard to the design of the present study.

First, this evaluation study is carried out in the routine youth care practice, which contributes to the ecological validity of the findings. In addition, the use of an active control condition (care as usual) under real life conditions gives more insight in the unique contribution of NP compared to standard youth care interventions. This information is crucial for practitioners, policy makers and politicians in order to determine which prevention programs can best be implemented.

A second strength is the examination of potential moderators and mediators. We focus on moderators, such as ethnicity, age and gender. Moderator analyses establish under which circumstances interventions are effective in reducing problem behaviour (Clingempeel & Henggeler 2002). Through this method we could detect whether NP is effective with older or younger adolescents, boys or girls, and with adolescents from different ethnic backgrounds. Further, our study includes diverse secondary outcome measures (e.g., cognitive distortions) leading to a better understanding of processes that could mediate the relation between the intervention and delinquent behaviour.

Third, when examining the effects in terms of delinquent behaviour we distinguish between involvement in, frequency and seriousness of delinquent acts. These specific measures of criminal offending contribute to a more detailed view on program effectiveness (Farrington & Welsh 2005). Moreover, the investigation of long-term effects up to one year after the intervention could identify possible sleeper effects.

Finally, the role of general treatment factors, such as the therapeutic alliance, are also taken into account. This will lead to a better understanding of the influence of non-specific treatment factors on the program effects, and the unique effects of specific treatment factors over non-specific treatment factors.

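### With 180 participants, the planned interaction test does not reach the stated power above 0.80 for small moderator effects

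*Protocol article*

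**What the plan says.** The Sample size section first justifies the main comparison: "Power calculations indicated that 90 adolescents per condition" are enough, "assuming an alpha of 0.05, 0.95 power, and a medium effect size". It then says the same sample is sufficient for moderator analyses, with "Power > .80 to detect small effects for 2 to 8 groups", and concludes that "a total of 180 adolescents and parents will be included". The Design section adds that "The ratio of the randomization between NP and CAU is 1:1".

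The Statistical analysis section defines the test to which the moderator power must apply: "Moderator analyses will be conducted using two-way ANCOVA’s with the moderators and treatment condition as factors, to examine interaction effects". Outcomes are analysed at post-test and follow-up with the pre-test score as covariate. The Aim of the study section names age, ethnicity and gender as moderators. The Discussion counts this as a strength: "Through this method we could detect whether NP is effective with older or younger adolescents, boys or girls".

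The article gives no numeric value for a small or medium effect, no pre-test correlation, and no definition of groups (cells of the layout or levels of the moderator).

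**The concern.** The two power statements sit badly together. A total of 180 is offered as what is needed for a medium main effect at 0.95 power, and the next sentence claims more than 0.80 for small effects in up to eight groups. In the usual F-test framework, an interaction with one degree of freedom has no more power than a main effect of the same f. Each further degree of freedom lowers it. A sample sized for a medium main effect therefore cannot be expected to detect small interactions.

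Subgroup differences are a stated aim. A reader who accepts the sentence will take the risk of missing a small interaction to be below 20%. If the true risk is several times that, a non-significant interaction carries little information about whether the programme works alike for boys and girls, younger and older adolescents, or different ethnic groups.

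**Working it through.** **Inputs from the article.** N = 180, 1:1 allocation, alpha 0.05, a two-way ANCOVA interaction test, and the pre-test as covariate.

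**Assumptions, because the article gives no figures.** Small is f = 0.10 and medium is f = 0.25 (d = 0.5). The pre-test correlation r is varied. All 180 are analysed.

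**The article's main-effect figure.** For d = 0.5 and 0.95 power, a one-sided test needs 87–88 per arm, so 90 reproduces the figure (power about 0.96). A two-sided test with 90 per arm gives about 0.92. Reading medium as d = 0.5 is therefore consistent with the article's own calculation.

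**Formula for the moderator test.** Noncentral F with L moderator levels:
- numerator df = L − 1
- denominator df = 180 − 2L − 1
- λ = N f² / (1 − r²), with f scaled to the unadjusted SD

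**Noncentrality.**
- f = 0.10, r = 0: λ = 180 × 0.01 = 1.8
- f = 0.10, r = 0.5: λ = 1.8 / 0.75 = 2.4
- f = 0.10, r = 0.7: λ = 1.8 / 0.51 = 3.5
- f = 0.25, r = 0: λ = 180 × 0.0625 = 11.25

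**Power at N = 180.**

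| Moderator levels (cells) | f = 0.10, r = 0 | f = 0.10, r = 0.5 | f = 0.10, r = 0.7 | f = 0.25, r = 0 |
|---|---|---|---|---|
| 2 (4) | 0.27 | 0.34 | 0.46 | 0.92 |
| 3 (6) | 0.20 | 0.26 | 0.37 | 0.85 |
| 4 (8) | 0.17 | 0.22 | 0.31 | 0.80 |
| 8 (16) | 0.12 | 0.15 | 0.22 | 0.65 |

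Reading the sentence as a one-way comparison of 2 to 8 groups gives the same r = 0 values, 0.27 down to 0.12.

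**More generous variants for a small effect, two to eight levels.**
- f² = 0.02 in place of 0.01: 0.47 to 0.22
- alpha 0.10, f = 0.10: 0.38 to 0.21
- r = 0.8: 0.60 to 0.30
- r = 0.9: 0.87 for two levels, but 0.79 for three and 0.56 for eight

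**What 0.80 power would take (r = 0).** For f = 0.10, N is about 787 for two levels, 1,095 for four and 1,443 for eight. At N = 180 the smallest detectable f is 0.21, 0.25 and 0.29 respectively. In a balanced 2 × 2 layout the difference between the two subgroup treatment effects is 4f SDs. So f = 0.21 means effects differing by 4 × 0.21 = 0.84 SD, while f = 0.10 means 0.40 SD.

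**A model that does reproduce the claim.** A repeated-measures group-by-time test has λ = N f² m / (1 − ρ). With m = 4 waves and ρ = 0.7, λ = 1.8 × 4 / 0.3 = 24, and power runs from 0.99 (2 groups) to 0.84 (8 groups). At ρ = 0.5, λ = 14.4, and it runs from 0.90 to 0.56.

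**The case against.** The strongest counter-argument is that the sentence can be reproduced as worded, with small effects, from a repeated-measures power procedure using the trial's four waves and a correlation of about 0.7. That may be where it came from. It does not rescue the claim: the Statistical analysis section plans ANCOVAs at post-test and follow-up, and a group-by-time test would not by itself test treatment by moderator. It does, however, undercut a tempting inference, that small is a slip for medium. The medium reading fits only if groups means cells: at f = 0.25, four levels (eight cells) give 0.80, but eight levels give 0.65. The article does not show which explanation is right.

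Second, a reader might quote 12–27% as the true power. That ignores the pre-test covariate the plan specifies, and the 12% end needs eight moderator levels. With eight cells the low end is 17%. Any single figure rests on an f and an r that the article does not state, so a range is needed.

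Third, a reader might infer that null interactions will be reported as equal effectiveness. No sentence says so. The Discussion speaks only of detecting for whom the programme works. Misreading is a risk, not something planned.

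Finally, age need not be entered as continuous. The Background describes separate programme modalities below and from 16 years, so age as a factor has a rationale.

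These points narrow the concern. They do not bring the planned test to 0.80 for small effects across 2 to 8 groups under any ANCOVA variant tried.

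**Conclusion.** The power statement is wrong as written for the planned analysis. For a small interaction (f = 0.10, alpha 0.05, all 180 analysed), power is about 0.17–0.27 in layouts of four to eight cells without covariate gain. It is at most about 0.46 with a pre-test correlation of up to 0.7. The chance of missing such an interaction is therefore roughly 54–83% (1 − 0.46 to 1 − 0.17), where the article implies less than 20%. If eight groups means eight levels, power is 0.12–0.22 over the same correlations.

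The sample does support a claim about medium interactions: 0.92 for two levels and 0.80 for four, before any gain from the pre-test. The conclusion rests on conventional values for small and medium and on an assumed range for r. It holds for every such value tried except the two-level moderator at r = 0.9. The error concerns the moderator aim and leaves the main comparison untouched.

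**What to change.** Restate the moderator sentence in the Sample size section for the test actually planned, giving f, the interaction degrees of freedom and the assumed pre-test correlation. For example: with 180 participants and alpha 0.05, the interaction test has power of at least 0.80 for medium interactions (f = 0.25) in layouts of up to eight cells. For small interactions (f = 0.10), power is roughly 0.17–0.46 for pre-test correlations of 0 to 0.7. If a repeated-measures model was the source of the stated figure, say so and do not apply it to the ANCOVA.

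Add to the Statistical analysis section that interaction estimates will be reported with 95% confidence intervals, and that a non-significant interaction is not evidence of equal effects across subgroups. Bring the Discussion's statement about detecting subgroup effects into line. Using age as a continuous moderator is optional.

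The cost is wording and a weaker moderator claim. Sample size, allocation and the primary analysis do not change.
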